### Data collection

2.7

The patients enrolled in the group will receive clinical or laboratory assessments (Table 1) during the screening period, the drug infusion period, on the first day after the end of trial interventions, and on the 28th day after enrollment. Before treatment (D0; screening period), the following indicators should be evaluated: pathogen culture results, the level of blood 5-HT, acute physiology and chronic health evaluation (APACHE II) scores, and SOFA scores. Before treatment (D0; screening period), on the third day of treatment (D2), and on the first day after treatment (D4), the following indicators will be measured: immune function indicators (white blood cell count, peripheral lymphocyte count, CD4+ and CD8+ T-cell count), renal injury indicators (Cys C), inflammation Indicators (the level of IL-6, CPR, ESR, SOD), and infection indicators (the level of serum PCT, fungi (1,3)-beta-D-Glucan, galactomannan antigen). Daily assessment indicators include the following: liver injury indicators (the level of ALT, AST, total bilirubin, direct bilirubin), the level of blood lactate, renal injury indicators (the level of Cr, BUN), lung injury indicators (oxygenation index, not applicable during extracorporeal membrane oxygenation (ECMO) support), fluid balance, vasoactive drug dose, urine volume, SOFA scores, and concomitant medications that may affect the outcome. Other indicators are the duration of organ function replacement therapy including continuous renal replacement therapy (CRRT), ECMO and mechanical ventilation, the incidence of new dysfunction, ICU stay time, ICU mortality, and 28-day mortality. Safety indicators include adverse reactions and the incidence of serious adverse events. Among them, the 28-day survival information of patients will be obtained by telephone follow-up. For dropout events, the causes will be recorded in detail and these patients will also be followed up. All the laboratory outcomes will be taken from the Central Laboratory of Zhujiang Hospital, and all the indicators needed to calculate the APACHE II score and SOFA score will also be recorded in detail. Furthermore, during the course of treatment, any out-of-plan evaluations of the above indicators by the treating physicians also will be collected. All of the above data will be collected by highly trained clinical observers.

**Table 1 T1:**
[figure not shown]
Schedule of clinical or laboratory assessments.

A specially designed case report form (CRF) will be used for data collection. The data will be collected by clinical observers. One observer will record the data first, and at least one observer will check the recorded data. The data is then recorded on web-based electronic CRFs on www.cloud.medsci.cn. To protect patient privacy, the CRF tables will only record patient initials and enrollment numbers as identifiers.

### Outcome measurement

2.8

#### Primary outcome

2.8.1

The primary outcome measure is the all-cause mortality rate at 28 days after enrollment.

#### Secondary outcome

2.8.2

The secondary outcome indicators mainly include the following aspects:

Requirements for organ function support: the duration of organ function replacement therapy including CRRT, ECMO, and mechanical ventilationImprovement of organ function: the changes in SOFA score; creatinine, transaminase, and cystatin after interventions completion; lactate clearance after interventions completion; and the incidence of new organ dysfunctionImprovements in infection indicators: the changes in PCT after interventions completion, PCT clearance after interventions completion, and changes in fungi (1,3)-beta-D-Glucan and galactomannan antigen after interventions completion.Improvement of inflammatory indicators: the changes in IL-6, ESR, SOD, and CRP after interventions completionImprovement of immune function indicators: the changes in lymphocyte count, white blood cell count, and CD4+ and CD8+ T cell count after interventions completion.The incidence of new organ dysfunction: the incidence of new acute liver injury, kidney injury, and lung injury. New organ failure refers to organ failure that occurs after enrollment.Other indicators: ICU length of stay (LOS).Additionally, we will also collect blood 5-HT levels before and after completion of the treatment to determine if there is a correlation between 5-HT levels and the prognosis of sepsis.

#### Adverse events and serious adverse events

2.8.3

Granisetron has mild side effects in healthy people. Common side effects include headache (10%–15%), constipation (2%–4%), lethargy (2.5%–5%), diarrhea (0.6%–2%), and dizziness (0.5%–3.2%).^[14]^ According to reports, the 5-HT3 receptor inhibitor may also prolong the QT interval of the heart, but this is very rare.^[16]^ However, reports of side effects in granisetron in critically ill patients are lacking. Therefore, this study will also focus on the possible adverse effects of using granisetron for patients with sepsis. Observers will dynamically record treatment-related side effects daily, including headache, constipation, bloating, diarrhea, nausea, vomiting, arrhythmia, and other side effects that treatment physicians believe are related to the study. The time and frequency of the side effects should be recorded in detail and reported to a specialized expert group on side effects, which consists of three senior physicians dealing with critically ill patients, who will judge the correlation between adverse events and research interventions.

A serious adverse event is any event that meets the following criteria within 28 days of the start of the study: results in death; is life-threatening; results in prolongation of the patient's hospitalization period; or results in a persistent or significant disability.

Any serious adverse events that occur during the trial should be recorded. If it is determined as relevant to the study, the study interventions will be immediately stopped, and the necessary treatment for serious adverse events will be taken and immediately reported to the Ethics Committee. Researchers in the GRANTISS study group and all the treating physicians should undergo training prior to the start of the study to be able to accurately identify serious adverse events.

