#### Safety analysis

2.12.12

The incidence of adverse events will be compared using the chi-square test. The adverse events that occur in the trial will be listed. For the quantitative indicators, the corresponding difference test method will be used to compare between groups or compare within groups.

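### Non-serious adverse events are recorded through a relatedness filter applied by staff not stated to be blind, so the planned between-arm test of adverse-event incidence can be distorted

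*Protocol article*

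**What the plan says.** Section 2.8.3 (Adverse events and serious adverse events) sets the daily recording rule: "Observers will dynamically record treatment-related side effects daily". It names seven symptoms, from headache to arrhythmia, and then adds "other side effects that treatment physicians believe are related to the study". Recorded side effects go to a group of three senior physicians, "who will judge the correlation between adverse events and research interventions". Section 2.7 (Data collection) uses similar causal language: "Safety indicators include adverse reactions and the incidence of serious adverse events".

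Serious events are handled differently. Section 2.8.3 says: "A serious adverse event is any event that meets the following criteria within 28 days of the start of the study". It adds: "Any serious adverse events that occur during the trial should be recorded". Neither sentence carries a causality condition.

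Section 2.12.12 (Safety analysis) then says: "The incidence of adverse events will be compared using the chi-square test". It also promises a listing of the adverse events that occur, with no limit to related ones.

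Section 2.5 (Blinding) calls the trial single-blind and names three parties as blind: subjects, their relatives and the statisticians. It describes a matching saline placebo, the same type of syringe and one common label.

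**The concern.** The analysis section speaks of the incidence of adverse events, while the collection section speaks of side effects already considered related to treatment. These are different quantities. In septic intensive-care patients most symptoms have several possible causes, so what is recorded depends heavily on who judges relatedness and what that person knows.

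Safety is part of the stated aim, and section 2.8.3 itself says that reports of granisetron side effects in critically ill patients are lacking. A causality screen before recording suits that situation poorly, because an unexpected effect is the one nobody is yet inclined to attribute to the drug. What is never recorded cannot be recovered by the expert group, by the data and safety monitoring board's six-monthly review of adverse events (section 2.10), or by any analysis plan.

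**Working it through.** The plan gives no figure on this point, so the check is a comparison of sections followed by an illustration.

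**Step 1: which events pass through the filter**

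| Type of event | Condition for recording | Source |
|---|---|---|
| Serious | None on causality | 2.8.3 |
| Non-serious, one of the seven named symptoms | Ambiguous: introduced as treatment-related, but named individually | 2.8.3 |
| Non-serious, any other | Treating physician believes it related | 2.8.3 |

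The third row covers more than unforeseen events. Section 2.8.3 gives lethargy (2.5% to 5%) and dizziness (0.5% to 3.2%) as common granisetron side effects, and neither is among the seven. Both therefore depend on the physician's belief.

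**Step 2: who applies the filter.** Treating physicians and observers do. Neither is on the section 2.5 list of blinded parties, and nor is the expert group. Under section 2.4 the clinical screeners open the allocation envelope. The protocol neither states that physicians and observers know the arm nor says that they are kept from knowing it.

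**Step 3: illustration of an arm-dependent filter.** Inputs from the protocol: 77 patients per arm (2.11) and a two-sided 0.05 Pearson chi-square test (2.12.2, 2.12.12). Assumptions, not in the protocol: a true event rate t equal in both arms, and recorded shares q_G (granisetron) and q_C (control).

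The recorded rates are p_G = t × q_G and p_C = t × q_C. With recorded counts x_G and x_C, n = 77 and p̄ = (x_G + x_C)/(2n), the statistic is

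X² = (x_G/n − x_C/n)² / [p̄(1 − p̄)(2/n)].

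The test rejects when X² > 1.96² = 3.84. The rejection probability is the sum of Bin(x_G; 77, p_G) × Bin(x_C; 77, p_C) over all rejecting pairs. For example, t = 0.20, q_G = 0.8 and q_C = 0.4 give p_G = 0.16, p_C = 0.08 and a rejection probability of 33.7%.

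| True rate, both arms | All recorded | 50% / 50% | 80% / 60% | 80% / 40% | 80% / 20% |
|---|---|---|---|---|---|
| 10% | 5.1% | 4.9% | 8.0% | 18.1% | 40.7% |
| 20% | 5.1% | 5.1% | 11.2% | 33.7% | 73.9% |
| 30% | 5.0% | 5.2% | 15.0% | 50.3% | 90.8% |
| 40% | 5.3% | 5.1% | 19.7% | 65.2% | 97.5% |

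(Column headings after the second give the recorded shares, granisetron / control.)

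**Step 4: a filter that acts equally in both arms.** The 50% / 50% column shows that the false-positive rate stays near 5%, but real differences are harder to see. With assumed true rates of 40% and 20%, power is 78.2% with full recording. It is 42.2% if half of events are recorded (0.20 against 0.10) and 22.3% if a quarter are (0.10 against 0.05).

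**The case against.** The case on the other side has several parts.

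- **Serious events are outside the filter.** A reader might infer that every adverse event needs a causality opinion to be recorded, so that the safety test compares opinions and not events. The protocol does not support this. Deaths, life-threatening events and prolonged hospitalisation are recorded whatever their cause. New acute liver, kidney and lung injury (2.8.2) and the scheduled laboratory values (2.7) are collected too. This stands in full.
- **The seven symptoms may be a checklist.** Grammatically, the belief condition attaches only to the other side effects. An expert group that judges causality after recording would have little to do if only related events were recorded. The reading is reasonable, but the sentence still introduces the list as treatment-related. Arrhythmia and constipation are on the list, so they are poor examples of events lost to the filter.
- **Staff knowledge of the arm is not documented.** A reader might take it as fact that staff know who receives saline. The single-blind label and the list of blinded parties make this plausible, but matched syringes and a common label point the other way. An arm-dependent bias needs that knowledge; the loss of power does not.
- **The figures are assumed.** A reader might be drawn to a headline relative risk. If recording is twice as complete in one arm, the false relative risk is 2 by construction, which is no evidence about this trial. The same limit applies to the table above.
- **A journal article condenses the full protocol.** The full collection rules may be better, and the assessment schedule in Table 1 is not visible. However, the article does not simply omit a rule. It states one explicitly and uses similar causal language in a second section.

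**Conclusion.** The point holds for non-serious adverse events. It is clearest for those off the seven-symptom list, including lethargy and dizziness; for the seven themselves the wording is ambiguous. As written, the record does not supply the quantity that section 2.12.12 proposes to compare and list.

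If physicians or observers know the arm, the comparison can be biased. If they do not, it still loses power for unexpected non-serious harm. The direction and size of any bias cannot be determined from the protocol. The illustrative false-positive rates, from 8.0% to 97.5% across the unequal recording shares tried, rest wholly on assumed event rates and shares and show only that the mechanism can matter with 77 patients per arm. The comparison of serious adverse events is not affected. This is a worthwhile, inexpensive correction and does not make the whole safety analysis invalid.

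**What to change.** In sections 2.7 and 2.8.3, replace the causal terms with one rule: record every adverse event in both arms, whatever its suspected cause. Use the seven named symptoms plus lethargy and dizziness as a solicited checklist, and add any other untoward event.

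In section 2.12.12, state that the between-arm comparison and the listing use all recorded adverse events.

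Have the existing three-physician group judge relatedness afterwards, without knowledge of the arm, and report its judgements as a secondary description.

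The cost is more case report form entries for observers who already record daily, and event reports to the expert group that do not show the arm. Blinding the recorders alone would not be enough, because a filter applied equally in both arms still discards events.

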### Interventions

2.6

The recruited patients will begin the trial intervention within 8 hours after randomization. Patients in the granisetron-treated group will receive granisetron 3 mg (PKU HealthCare Corp, Ltd) diluted to 25 mL with 22 mL of saline and intravenously administered within 10 minutes. Patients in the placebo group will receive 25 mL of normal saline and administer it intravenously within 10 minutes. The trial intervention will be administered at a frequency of 8 hours, with a course of treatment of 4 days or ICU discharge, whatever comes first. Considering the fluctuation of vital signs such as body temperature and blood pressure at different time points in 1 day, to avoid the influence of the abovementioned confounding factors on the trial results, it is stipulated that the trial intervention for each patient will be held at 12:00, 20:00, and 04:00. In addition to the trial intervention, patients will receive routine standard care and routine sepsis treatment according to the 2016 International Management Guidelines for Sepsis,^[7]^ including but not limited to the use of antibiotics, venous fluid resuscitation, use of blood products, enteral or parenteral nutrition, prevention of deep vein thrombosis, and supportive treatment for organ dysfunction. All treatments except study interventions will be determined by the treating physician and will be noted in detail in patients’ medical records.

For patients who may require using antiemetics, any antiemetics that act on 5-HT receptors should be avoided, but other classes of antiemetics such as metoclopramide may be used. Additionally, in the treatment of patients with sepsis, some liver-protective drugs such as reduced glutathione are often used to reduce septic liver damage; because the role of granisetron for liver function protection in clinic is not certain, the use of such drugs to alleviate organ dysfunction by the treating physician will be allowed, but the name, frequency, and dosage of the drug used should be accurately recorded.

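### The serious adverse event list covers a prolonged hospital stay but not a new or repeat admission, so events within 28 days whose only serious consequence is readmission are not counted as serious

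*Protocol article*

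**What the plan says.** Section 2.8.3 sets both the window and the criteria: "A serious adverse event is any event that meets the following criteria within 28 days of the start of the study". The criteria are "results in death; is life-threatening", then "results in prolongation of the patient's hospitalization period", "or results in a persistent or significant disability". The last item is joined by *or* and closes the list. Nothing in the article adds new or repeat admission.

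The other relevant statements are:

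- **Treatment period (2.6).** Dosing is given "with a course of treatment of 4 days or ICU discharge, whatever comes first".
- **Recording (2.8.3).** "Observers will dynamically record treatment-related side effects daily", and "Any serious adverse events that occur during the trial should be recorded".
- **Day-28 contact (2.7).** "the 28-day survival information of patients will be obtained by telephone follow-up". The same section names SAE incidence as a safety indicator.
- **Use of the data.** The data and safety monitoring board reviews adverse events and SAEs every 6 months (2.10). Section 2.12.12 compares adverse event incidence by chi-square test and lists the events. It names no separate test for SAEs.

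**The concern.** The window and the hospitalization criterion do not fit each other. The window can run on after a patient has left hospital, but the criterion works only while the patient is still an inpatient. A patient who goes home and is readmitted before day 28 has had an event with a plain hospital consequence, yet nothing in the list makes that consequence serious.

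Safety is one of the trial's two stated aims, and 2.8.3 itself says that side-effect reports for granisetron in the critically ill are lacking. Death is already the primary outcome, so what the SAE count adds is mainly non-fatal harm, and that is where the gap lies. The classification also has consequences. Under 2.8.3 an SAE judged related to the study is reported at once to the Ethics Committee, and an event that never qualifies as serious does not take that route.

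**Working it through.** The article states no SAE rate, discharge rate or readmission rate, so no figure of the plan's own can be reproduced on this point. The check is a reading of the rule, followed by an illustration under stated assumptions.

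**Step 1: test the case against the list.** Take a survivor discharged before day 28 and readmitted within the window. The event is neither fatal nor life-threatening and leaves no lasting disability.

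| Criterion in 2.8.3 | Met? |
|---|---|
| Death | No |
| Life-threatening | No |
| Prolonged hospitalization | No: the stay had ended |
| Persistent or significant disability | No |

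The event is not an SAE under the rule as written. If the event is fatal, life-threatening or disabling, it still qualifies. If the patient is still in hospital, the prolongation criterion applies and nothing is lost.

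**Step 2: can the case arise?** Treatment lasts at most 4 days (2.6) and the window lasts 28 days (2.8.3). Read as running from each patient's start, that leaves at least 28 − 4 = 24 days after the last dose. Discharge and readmission can both fall in this period. How often they do, the article does not say.

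**Step 3: illustrate the undercount.** Arm size is 77 (2.11). Missed patients per arm = 77 × assumed proportion with a readmission-only event:

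- 2%: 77 × 0.02 = 1.5
- 5%: 77 × 0.05 = 3.9
- 10%: 77 × 0.10 = 7.7

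**Step 4: illustrate the effect on the arm difference.** Hidden difference = granisetron proportion − control proportion, with control assumed at 5%:

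- Equal proportions: 5% − 5% = 0 points
- Doubled on granisetron: 10% − 5% = +5 points
- Halved on granisetron: 2.5% − 5% = −2.5 points

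The SAE count can only fall. The difference between arms can move either way or not at all.

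**Step 5: an upper bound based on survivors.** Read the 20% difference in 2.11 as 33% versus 13% mortality. That reading fits the stated sample size: the unpooled two-proportion formula at two-sided 0.05 and 80% power gives 66 per arm, and 66 × 1.15 gives 76 per arm (152 in total) while 66 / 0.85 gives 78 per arm (156), against the stated 154. Survivors are then 77 × 0.67 = 52 and 77 × 0.87 = 67. An assumed 5% to 15% of these is 2.6 to 7.7 and 3.3 to 10 events. With the same rate per survivor, the arm with more survivors loses about 0.8 to 2.3 more events, or 1 to 3 percentage points of 77. These are upper figures for the assumed rates, because they treat every survivor as discharged early enough to be readmitted and every readmission as missed.

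**The case against.** The best case for leaving the text alone has four parts.

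1. **Few patients may be exposed.** These are ICU patients with organ dysfunction, and many may still be in hospital at day 28. The article gives no length of stay, so it does not show that many go home early. This stands, and it is why no size can be fixed.
2. **The stated test is on adverse events.** The SAE list decides only whether an event is called serious, not whether it is an adverse event, and 2.12.12 compares and lists adverse events. This also stands: the gap bears on SAE incidence and SAE reporting, and not directly on that test. Two limits apply. Daily recording is described for treatment-related effects, and the day-28 contact is described only for survival, so nothing described prompts the recording of a readmission.
3. **The article is condensed.** Telephone scripts and case report form fields belong in the full protocol, and the assessment schedule (Table 1) is not shown. The call may ask more than survival. That is fair for the call. It does not cover the definition, which the article states in working form with its window and closed list.
4. **Stronger readings go too far.** A reader might infer that every readmitted patient is lost, or that the safety comparison is biased. The documents support neither. Fatal, life-threatening or disabling readmissions still count. An undercount common to both arms leaves the difference unchanged, and the article has no data from which unequal rates could be shown.

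**Conclusion.** The point holds as a gap in the definition. Followed as written, 2.8.3 does not class as serious an event within 28 days whose only serious consequence is readmission, so SAE incidence may be undercounted in a safety indicator that the monitoring board reviews.

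The number of events affected is unknown. The range of about 1.5 to 7.7 patients per arm rests wholly on the assumed 2% to 10%, and the survivor-based figures are an upper bound under their own assumed rates. Distortion between the arms is possible but not demonstrated. The primary outcome, 28-day all-cause mortality, is untouched. This is a minor but worthwhile correction.

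**What to change.** In 2.8.3, replace the hospitalization criterion with: *results in new or repeat inpatient hospitalization or prolongation of the existing hospitalization*. Add a question on readmission since discharge to the day-28 telephone contact already planned in 2.7, so that the wider criterion can be applied to patients who have gone home.

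The cost is one phrase and one question. The downside is a few more SAE reports to record and judge for relatedness. Sample size, primary outcome and treatment schedule do not change.
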